**Fig. 1 Fig1:**
[figure not shown]
Trial flowchart (protocol v1.1, 13 July 2021)

### Primary outcome measure

The primary outcome measure is the duration of mechanical ventilation. The primary outcome measure is the duration of mechanical ventilation from enrolment to the study until successful extubation. Extubation failure is defined as the need for reintubation within 48 h. For infants who fail extubation, they continue in their initial study arm if they are less than 28 days old, and the time they remain ventilated is counted towards the total duration of mechanical ventilation. For infants that remain ventilated beyond day 28 of life, the study continues till their first extubation attempt, and that period represents the primary outcome measure. Currently at KCH, the CLAC algorithm is used only for mechanically ventilated infants and in the context of clinical research studies. Hence, automatic oxygen control will be discontinued following extubation. Non-invasive ventilation modes will be delivered via the SLE6000 ventilators, and the control of the inspired oxygen concentration will be performed manually.

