### Sample size

In a cohort of 368 preterm infants born between 24 to 30 weeks of gestation, the standard deviation for the duration of mechanical ventilation was 3.83 days [27]. The median duration of ventilation in our NICU was 12 days (mean 19 days). Randomisation of 70 infants allows us to detect a decrease in the duration of mechanical ventilation of three days with a 90% power at the 5% significance level.

At the request of the ethics committee, an interim analysis will be carried out after half the sample has been recruited to review if enough data have been gained at that point. The analysis will be performed by an independent researcher not involved in the project to avoid introducing bias to our data. The research team will be blinded to the results of the interim analysis unless there are any significant findings.

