### Statistical analysis

Data will be compared between infants in the intervention group (closed-loop automated oxygen control) and infants in the control group (manual oxygen control). The data will be assessed for normality; Student’s *t* test will be used for normally distributed data and Mann-Whitney *U* test for skewed data. Categorical data will be assessed using the Fisher two-tailed exact test. Analysis will be undertaken using SPSS software (SPSS Inc., Chicago, IL, USA). Data analysis will be conducted on an intention-to-treat basis, and missing data will not be imputed. Analysis will be undertaken to a researcher blind to which arm the infants was randomised.

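### The primary outcome and analysis rules give no valid value to an infant who dies while ventilated, and mortality is not a named outcome

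*Protocol article*

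**What the plan says.** Under Primary outcome measure the article states: "The primary outcome measure is the duration of mechanical ventilation from enrolment to the study until successful extubation". Failure has one criterion: "Extubation failure is defined as the need for reintubation within 48 h". Two situations get their own rule. An infant under 28 days old who fails extubation stays in the allocated arm and goes on accruing ventilated time. For later cases, "For infants that remain ventilated beyond day 28 of life, the study continues till their first extubation attempt". Death has no rule.

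Under Statistical analysis the options for a continuous outcome are Student's t test for normal data or the "Mann-Whitney *U* test for skewed data". The same section adds: "Data analysis will be conducted on an intention-to-treat basis, and missing data will not be imputed".

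Mortality is not among the outcomes in the Abstract, the Trial registration dataset, the Background or Secondary outcomes. Retinopathy is to be reported although it is not a secondary outcome; death has no such line. The Background does link hypoxia, which the intervention aims to reduce, to mortality.

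**The concern.** Duration of ventilation is measured in infants who can die before the measurement is complete. An infant who dies ventilated never reaches the end point that defines the outcome, so the analyst has to choose a rule. The stated rules leave two obvious ones:

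- Treat the value as missing. It is not imputed, so the infant drops out and the comparison no longer covers everyone randomised.
- Stop the clock at death. An early death then becomes a short duration, which is the result the trial hopes to see.

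The definition of failure raises a related question. An infant who dies within 48 h of extubation without being reintubated is neither clearly a failure nor clearly a success.

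At stake is the direction of the primary comparison whenever mortality differs between arms. The trial is open-label, and the interim review looks at the same endpoint, so the rule should be settled before anyone sees outcomes by arm.

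**Working it through.** **1. The plan's own figure.** Inputs from Sample size: SD ("the standard deviation for the duration of mechanical ventilation was 3.83 days"), a 3-day difference, 90% power, 5% level (taken as two-sided, which reproduces the stated size) and 1:1 allocation.

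n per arm = 2(1.960 + 1.282)² × 3.83² / 3² = 34.25, rounded up to 35, or 70 in total. Power at 35 per arm = Φ(3 / (3.83√(2/35)) − 1.960) = Φ(3.277 − 1.960) = 0.906. The stated 70 reproduces, with no allowance for deaths.

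**2. Power if deaths are dropped equally.** With 10% deaths in each arm, 31.5 infants per arm remain: Φ(3.109 − 1.960) = 0.875. At 20% deaths it is 0.834.

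**3. Bias if deaths are unequal.** The documents give the unit's median (12 days) and mean (19 days). Assumptions: a lognormal shape; no true effect; deaths of 10% in one arm and 20% in the other; death times uniform over days 0-10; and a correlation ρ between risk of death and the (log) duration the infant would otherwise have had.

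σ = √(2 ln(19/12)) = 0.959. For death proportion d, let c = Φ⁻¹(1 − d) and P = Φ(c − ρσ).

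- Mean with deaths dropped = 19P / (1 − d)
- Mean with the clock stopped at death = 19P + 5d

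| ρ | P at 10% | P at 20% | Dropped: 10% v 20% arm | Difference | Clock stopped: 10% v 20% arm | Difference |
|---|---|---|---|---|---|---|
| −0.3 | 0.9417 | 0.8706 | 19.9 v 20.7 | −0.8 | 18.4 v 17.5 | +0.9 |
| 0 | 0.9000 | 0.8000 | 19.0 v 19.0 | 0.0 | 17.6 v 16.2 | +1.4 |
| 0.3 | 0.8399 | 0.7102 | 17.7 v 16.9 | +0.9 | 16.5 v 14.5 | +2.0 |
| 0.6 | 0.7600 | 0.6050 | 16.0 v 14.4 | +1.7 | 14.9 v 12.5 | +2.4 |

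A positive difference (days) means the arm with more deaths looks better. Simulated trials give about −0.7 to +1.7 days with deaths dropped and about 1.0 to 2.4 days with the clock stopped. The formulas agree to within simulation error and small differences in how death times are drawn; their lower ends at ρ = −0.3 are −0.8 and 0.9. If mortality is equal, both arms shift by the same amount and the difference is zero.

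**4. Effect on the Mann-Whitney test** (simulation, 35 per arm, 10% v 20% deaths, nominal 2.5% in each direction). The test wrongly favours the higher-mortality arm in:

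- about 5-12% of trials with the clock stopped at death;
- about 6% with deaths dropped and ρ = 0.6, and close to nominal when death is unrelated to severity;
- about 1% or fewer with death ranked worst.

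**5. A larger gap.** At 10% v 30% deaths and ρ = 0.6, dropping deaths gives means of 16.0 v 13.0 days. The false benefit of 3 days is as large as the design effect, and the wrong arm wins in 9.8% of trials.

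**The case against.** The article never says that these infants are excluded. It also calls the outcome simply the duration of ventilation, and an infant who dies ventilated does have an observed duration. That is fair, and it is why both readings are worked through above. It does not rescue the plan, because the observed duration is exactly the value that rewards early death.

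A reader might infer that deaths always flatter the arm that has more of them. The documents do not support that. Dropping deaths gives no bias when death is unrelated to severity and can reverse direction, and equal mortality biases neither reading. Nor does pairing intention-to-treat with no imputation amount to a contradiction. The pairing is common; what is missing is a rule for death.

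A reader might also conclude that dying soon after extubation counts as success, or worry about extubation when care is redirected. The first is only ambiguous: an infant dying of respiratory failure could be said to have needed reintubation. The second appears nowhere in the article, which describes extubation on readiness criteria.

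The size can be challenged too. The lognormal above implies an SD of about 23.3 days, so the standard error of a mean difference is 23.3 × √(2/35) ≈ 5.6 days, and a shift of 1 to 2.4 days is well under half of that. Setting such shifts against a 3-day target planned with SD 3.83 overstates them, and the error rates of the rank test are the better measure.

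Finally, an analysis plan that is not shown may deal with deaths, and serious adverse events are recorded with follow-up to discharge. But the end point, the failure definition, the tests and the missing-data rule are all fixed in this article. Any plan that scores every randomised infant sensibly would have to add to them or depart from them.

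**Conclusion.** The point holds in conditional form. The rules as written give no valid primary value to an infant who dies while ventilated, and leave death within 48 h of extubation ambiguous. Stopping the clock at death favours the higher-mortality arm throughout the range examined. Dropping deaths abandons part of the randomised comparison, and its bias may have either sign. The direction follows from the definitions. The size rests on assumed death rates, an assumed lognormal shape, assumed death times and an assumed link between death and severity, none of which the documents supply. This should be settled before any comparison by arm, because the choice of rule can change which arm looks better.

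**What to change.** - In a rank-based (Mann-Whitney) primary comparison, keep every randomised infant and give the worst rank to death before successful extubation, including death within 48 h of extubation. State the matching rule for infants still ventilated beyond day 28, whose outcome ends at the first extubation attempt.
- Add a supportive competing-risks analysis: cumulative incidence of successful extubation, with death as the competing event.
- Name death as an outcome and report it by arm.
- Apply the same rule at the interim analysis.

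The cost is wording, since deaths are already in the clinical record. The downside is that the primary result is no longer a pure difference in days, so duration among survivors should be reported alongside and labelled as a comparison of survivors only. Ventilator-free days would be another way to include deaths; what matters is that one rule is fixed in advance.

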**Methods:**

This randomised controlled trial performed at a single tertiary neonatal unit is recruiting 70 infants born at less than 31 weeks of gestational age and within 48 h of initiation of mechanical ventilation. Infants are randomised to CLAC or manual oxygen control from recruitment until successful extubation. The primary outcome is the duration of mechanical ventilation, and secondary outcomes are the percentage of time spent within target oxygen saturation ranges, the time spent in hypoxia or hyperoxia, the number of manual adjustments required, the number of days on oxygen, the incidence of bronchopulmonary dysplasia and the length and cost of neonatal unit stay. The study is performed following informed parental consent and was approved by the Yorkshire and the Humber-Sheffield Research Ethics Committee (protocol version 1.1, 13 July 2021).

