### Intervention

At enrolment, participants are randomised to receiving either closed-loop automated oxygen control (intervention group) or manual control of the inspired oxygen concentration. All infants are ventilated using the SLE6000 ventilators and ventilation settings are manually adjusted by the clinical team as per the unit’s protocol. In addition to standard care, infants in the intervention group are connected to the Oxygenie Auto-O_2_ software (SLE). This software uses oxygen saturation levels from the SpO_2_ probe attached to the neonate, which are fed into an algorithm, to automatically adjust the percentage of inspired oxygen to maintain oxygen saturations within the target range. Manual adjustments including the percentage of inspired oxygen are allowed at any point during the study, if deemed appropriate by the clinical team.

The nurse-to-patient ratio is according to the unit protocol that is determined on the patient’s acuity. Respiratory care will be provided for all infants by the clinical team as per the unit’s guidelines. All infants will be ventilated using the SLE6000 ventilators and ventilation settings will be adjusted manually following the unit’s protocol. The intervention will be performed in addition to standard care and manual adjustments will be allowed at any point during the study, if deemed appropriate by the clinical team (p10–11, 173–180).

Infants are studied from enrolment until successful extubation [25]. For infants who fail extubation and require reintubation within 48 h, they continue in their initial study arm if they are less than 28 days old. At KCH NICU, preterm infants with non-chronic respiratory pathology are extubated from a targeted tidal volume of 5 ml/kg, a peak inspiratory pressure at or below 18 cm H_2_O and a backup rate of 40 breaths per minute. FiO_2_ requirement should be less than 0.3. The infant should have good respiratory drive as well as blood gases. Therefore, for infants randomised to the intervention group, closed-loop oxygen delivery resumes. Preterm infants that remain ventilated beyond day 28 of life continue at their study arm (closed-loop automated oxygen control or manual oxygen control) till their first extubation attempt (see Fig. 1).

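### The primary outcome has two end points: successful extubation in general, but the first extubation attempt, successful or not, for infants still ventilated beyond day 28 of life

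*Protocol article*

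**What the plan says.** All statements are in the protocol article.

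- **Primary outcome measure, general rule:** "The primary outcome measure is the duration of mechanical ventilation from enrolment to the study until successful extubation". The same section adds "Extubation failure is defined as the need for reintubation within 48 h".
- **Primary outcome measure, failure before day 28:** such infants stay in their arm, and "the time they remain ventilated is counted towards the total duration of mechanical ventilation".
- **Primary outcome measure, beyond day 28:** "For infants that remain ventilated beyond day 28 of life, the study continues till their first extubation attempt, and that period represents". The sentence ends by naming the primary outcome, so this period is what is analysed. The attempt is not required to succeed.
- **Intervention:** the section opens by saying that infants are studied until successful extubation. It closes by keeping infants ventilated beyond day 28 in their arm "till their first extubation attempt (see Fig. 1").
- **Abstract, Methods:** "Infants are randomised to CLAC or manual oxygen control from recruitment until successful extubation", with no exception. The Discussion says the same.
- **Blinding:** the trial is open, and ongoing care is decided by the clinical team.
- **Statistical analysis:** t test or Mann-Whitney U test, by intention to treat. No step is given for infants whose attempt after day 28 fails.
- **Trial registration dataset:** follow-up runs to discharge from the neonatal unit.

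**The concern.** One outcome variable holds two quantities. Up to day 28 of life a failed extubation does not stop the clock, and re-ventilated time is added. After day 28 the first attempt stops it, so a failure and a success are scored alike. An infant who fails on day 27 can end with a longer recorded duration than one who fails on day 29 and then stays ventilated for weeks.

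Three features make this more than untidy wording.

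1. Being ventilated at day 28 is a post-randomisation state that the intervention is meant to change. The applicable definition can therefore itself depend on treatment.
2. The Background argues that closed-loop control may speed weaning of inspired oxygen, which it calls a major determinant of readiness for extubation. The intervention could thus bring attempts forward whether or not they succeed, and after day 28 an earlier failed attempt would be recorded as a shorter duration. The team timing the attempts knows the allocation.
3. Entry is tied to the start of ventilation, whereas the switch is tied to postnatal age. The listed criteria do not exclude an infant first ventilated late, who would meet the first-attempt rule early in the study. The article does not say how often this would occur.

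The wording also needs clarifying for an infant who failed before day 28 and is still ventilated after it, because a first attempt has already taken place.

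**Working it through.** **The plan's own figure.** Inputs from Sample size: SD 3.83 days, difference 3 days, 90% power, 5% significance (taken as two-sided), 1:1 allocation.

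n per arm = 2 × (1.960 + 1.282)² × 3.83² / 3² = 34.25, rounded up to 35, so 70 in total. The stated 70 reproduces. The calculation does not model the day-28 rule, so it neither supports nor refutes this point.

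**Infants under the second rule.** Inputs from Sample size: unit median 12 days, mean 19 days. The distribution is an assumption, so two are used.

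- Lognormal: mean/median = exp(σ²/2), so σ = √(2 ln(19/12)) = 0.959. P(duration > 28) = 1 − Φ(ln(28/12)/0.959) = 1 − Φ(0.884) = 0.188, and 0.188 × 70 = 13.2 infants.
- Gamma with the same median and mean: P(duration > 28) = 0.230, and 0.230 × 70 = 16.1 infants.

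A 28-day duration stands in for day 28 of life. Because the clock starts at enrolment, a cut-off of 26 to 27 days is also reasonable. It gives 0.210 to 0.199 under the lognormal, or 14 to 15 of 70.

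**Infants actually mis-measured.** If the attempt after day 28 succeeds, both rules give the same number. Only failures matter. The article gives no failure rate, so 20% to 50% is assumed.

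- Low end: 13.2 × 0.20 = 2.6.
- High end: 16.1 × 0.50 = 8.1.

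That is about 3 to 8 of 70.

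**Effect on the level of the mean.** Understatement = share × failure rate × uncounted days. With the lognormal share and an assumed 3 to 14 uncounted days:

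- 0.188 × 0.20 × 3 = 0.11 days
- 0.188 × 0.50 × 14 = 1.32 days

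This is a shift within an arm. If it is equal in both arms, it cancels from the difference.

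**Effect on the between-arm difference in means.** Bias = share × gap in failure rates × uncounted days, with the same share assumed in both arms. For an assumed 20-point gap:

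- 0.188 × 0.20 × 7 = 0.26 days
- 0.188 × 0.20 × 14 = 0.53 days

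That is about 0.3 to 0.5 days. The gamma share raises the upper value to 0.230 × 0.20 × 14 = 0.64 days. Swapping the arms reverses the sign.

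**Effect on the rank test.** Simulation: 35 per arm, lognormal (median 12, σ 0.959), cut-off 27 days, 10 uncounted days per failure, 6,000 runs per scenario.

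| Scenario | Mann-Whitney rejection, recorded duration | Full duration |
|---|---|---|
| No effect, 30% failure in both arms | 4.5% | 4.6% |
| No effect, 50% vs 30% failure | 4.4% | 4.5% |
| Duration ratio 0.75, 50% vs 30% | 22.3% | 21.8% |
| Duration ratio 0.5, 50% vs 30% | 83.0% | 82.6% |

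The t test moved by at most about 3 percentage points. The simulation does not model the intervention bringing failed attempts forward, and the documents give nothing with which to size that.

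**The case against.** The strongest defence is that the rule is deliberate. Primary outcome measure and the end of Intervention state it consistently, and it aligns the measured period with the time on allocated control. The Abstract is a condensation, and its sentence describes the allocation period. This stands in part: the rule is not a slip. But the article gives no reason for it, and Primary outcome measure itself makes the truncated period the outcome, so the two end points do not come from condensation.

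A second defence is that the planned test is hardly disturbed. A median of 12 with a mean of 19 implies skew, which points to the Mann-Whitney U test, and shortened durations mostly keep high ranks. This stands, except for the unmodelled route of earlier failed attempts. A comparison of means is more exposed.

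A third concerns the wording. A study cannot continue until an event already past, so the natural reading is the first attempt after day 28. That is probably what is meant. Fig. 1, which is not shown, may settle it. Clarification is enough.

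A reader might also object that reintubation after 48 h goes uncounted. That is simply the article's definition of failure, applied at every age. Preferring another is a matter of taste and is no part of this point.

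**Conclusion.** The point holds as a defect in the definition of the primary outcome. Two end points are in force, the choice between them depends on a post-randomisation state in an open-label trial, and a failed attempt after day 28 enters the analysis as a complete duration.

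The size is modest. About 13 to 16 of 70 infants would come under the second rule, and about 3 to 8 would be mis-measured. These figures rest on the fitted distributions and, for the latter, on an assumed 20% to 50% failure rate.

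Three stronger readings are not supported:

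- **That all infants ventilated beyond day 28 are cut short.** Only those whose attempt fails are.
- **That an understated mean can be set against the 3-day target.** The target is a between-arm difference, and equal truncation cancels from it. Bias needs failures or attempt timing to differ by arm. It is about 0.3 to 0.5 days in means under the assumed 20-point gap and 7 to 14 uncounted days.
- **That the rule favours closed-loop control.** Earlier failed attempts in that arm would do so, but the documents do not show that this will happen, and the direction cannot be determined from them.

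The case for change rests on having one clear primary outcome at little cost, not on demonstrated bias.

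**What to change.** Measure the primary outcome for every infant, at any age, as ventilated time from enrolment to the extubation followed by 48 h without reintubation. Take it from the clinical records. Infants are already followed to discharge and analysed by intention to treat, so the time can be obtained and counted.

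State this measurement rule separately from how long the allocated oxygen control is delivered. No view is taken here on the delivery period. Reconcile Abstract (Methods), Intervention, Primary outcome measure and Discussion so that they give one end point.

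Report the first-attempt definition as a sensitivity analysis. State there what a first attempt means for an infant who failed before day 28.

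The cost is a wording amendment and a little more record extraction. The sample size stays at 70, because none of its stated inputs changes. The drawback is that some counted time may fall after allocated control has ended, which is acceptable under intention to treat and is why the sensitivity analysis is useful.

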### Secondary outcomes

The secondary outcomes are the percentage of time spent within target oxygen saturation range, the time spent in hypoxia or hyperoxia, the number of manual adjustments required, the number of days on oxygen, the incidence of bronchopulmonary dysplasia at 36 weeks post menstrual age and the length and cost of neonatal unit stay. In line with the latest published evidence [10], our pulse oximetry oxygen saturation targets in preterm infants born at less than 31 weeks gestational age are 91 to 95% with alarm limits in the range of 90 to 98%. A researcher who is blinded to which arm the infant was randomised will undertake the analysis of the data. Retinopathy of prematurity will not be recorded as a secondary outcome, as our study is not powered to detect any significant differences in ROP outcomes between the two participating groups, but this outcome will be reported.

The order of study events is detailed in the Standard Protocol Items: Recommendations for Interventional Trials (SPIRIT) figure in Fig. 2. A SPIRIT checklist is also provided as an additional file and the protocol is based on the SPIRIT reporting guidelines [26].

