## Abstract

**Background:**

Many preterm infants require supplemental oxygen in the newborn period but experience frequent fluctuations of their oxygen saturation levels. Intermittent episodes of hypoxia or hyperoxia increase the risk of complications. Compliance with achievement of oxygen saturation targets is variable, and the need for frequent adjustments of the inspired oxygen concentration increases workload.

Closed-loop automated oxygen control systems (CLAC) improve achievement of oxygen saturation targets and reduce both episodes of hypoxia and hyperoxia and the number of manual adjustments. This study investigates whether CLAC compared with manual oxygen control reduces the duration of mechanical ventilation in preterm infants born at less than 31 weeks of gestation.

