Closed-loop automated oxygen control (CLAC) systems monitor SpO_2_ values in real-time to calculate and make an adjustment to the FiO_2_ patient delivery without any human intervention [15]. These systems may provide a solution for the low compliance with achievement of target oxygen levels and reduce the need for manual adjustments and hence the workload, as well as reducing complications. Several algorithms exist to calculate the FiO_2_ adjustment in relationship to the SpO_2_ changes in infants with different severities of respiratory disease [16]. An example is the Oxygenie Auto-O_2_ software (SLE) that uses a proportional-integral-derivative control algorithm, and it has been shown to be effective in improving compliance with target achievement in preterm infants, reducing episodes of hypoxia or hyperoxia and the need for manual adjustments to supplementary oxygen [17]. In a randomised crossover study, using that device we demonstrated that preterm ventilated infants experienced fewer prolonged desaturations during the closed-loop automated oxygen control period and spent an increased percentage of time within their target SpO_2_ range with fewer manual adjustments to the inspired oxygen concentration [18]. A review of 16 studies highlighted that the studies of CLAC were very heterogenous for design, population size and device used [15]. Moreover, the majority of those studies had a crossover design and limited data available for analysis. Two reviews emphasised that none of the previous studies had demonstrated whether the clinical outcomes of preterm infants were improved [15, 19]. A subsequent literature review including 18 studies [19] highlighted that CLAC was consistently associated with an increased percentage of time spent within the target oxygen saturation range with fewer manual adjustments to the FiO_2_ and was effective in infants on non-invasive respiratory support or mechanically ventilated at a range of postnatal ages. The results appear to be consistent for all the control algorithms [19] and across different SpO_2_ target ranges [20, 21]. In addition, previous studies demonstrated that CLAC could facilitate earlier weaning of the inspired oxygen concentration when compared to manual control [22, 23], which is a major determinant of an infant’s readiness for extubation. It is, therefore, possible and our hypothesis that use of CLAC would reduce the duration of mechanical ventilation

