### Blinding

The study is not blinded. Decisions regarding ongoing care, for example ventilator settings and interventions such as blood gases and chest radiographs, are made by the clinical team as per the neonatal unit’s guidelines.

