### Data collection

Demographic and outcome data will be collected from the clinical records and recorded under a unique study identifier number. Basic epidemiologic parameters such as gestational age at birth, birth weight, corrected gestational age, postnatal age and weight at study enrolment, use of antenatal steroids, mode of delivery, doses of surfactant administered, birth plurality and associated comorbidities that may impact on the duration of mechanical ventilation, for example patent ductus arteriosus and infection, will be recorded for each infant. Oxygen saturation and FiO_2_ data will be downloaded from the ventilators. Paper data will be stored in a locked filling cabinet. Patient de-identified electronic data will be stored in password protected computers and on encrypted devices.

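### The plan claims a blind analyst for all the data, but the manual-adjustment counts will in effect show which coded arm is closed-loop control, so the claim should be limited and the primary analysis locked first

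*Protocol article*

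**What the plan says.** The trial is open label: under Blinding, the protocol article says "The study is not blinded". Blinding is claimed for the analysis, in two places. Under Secondary outcomes: "A researcher who is blinded to which arm the infant was randomised will undertake the analysis of the data". Under Statistical analysis: "Analysis will be undertaken to a researcher blind to which arm the infants was randomised". Neither sentence restricts the claim to particular outcomes.

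The secondary outcomes include "the number of manual adjustments required, the number of days on oxygen", the percentage of time in the target saturation range, and time in hypoxia or hyperoxia. Under Data collection, "Oxygen saturation and FiO_2_ data will be downloaded from the ventilators".

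On what the device does to these data, the abstract says that such systems "reduce both episodes of hypoxia and hyperoxia and the number of manual adjustments". The Background reports that the group's own crossover study found more time in range "with fewer manual adjustments to the inspired oxygen concentration". The Intervention section says that the software changes FiO2 automatically in the CLAC group only, while staff may make manual changes at any time.

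For the choice of test, the Statistical analysis section says "The data will be assessed for normality", with a t test or a Mann-Whitney test to follow.

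**The concern.** An analyst can be blind to arm only if the data do not reveal it. Here one of the outcomes to be analysed is close to a direct measure of which method of oxygen control was used, and the protocol announces the direction of the difference in advance. If the arms carry neutral labels, a table of manual adjustments by label shows which label is CLAC. If every variable carries the same label, that one table unmasks all infants and all outcomes at once.

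Two things are at stake. First, a final report that repeats the claim would describe a protection which the design does not have for some outcomes. Second, the blind on the primary outcome, duration of ventilation, depends on what the analyst has already seen. In an open-label trial it is worth making sure that this blind is real.

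**Working it through.** **The plan's own figure.** Inputs from Sample size: difference 3 days, SD 3.83 days, power 90%, 5% level (taken as two-sided), 1:1 allocation. Per arm, n = 2(1.960 + 1.282)² × 3.83² / 3² = 2 × 10.51 × 14.67 / 9 ≈ 34.3, rounded up to 35, so 70 in total. The stated 70 reproduces. Nothing below alters it.

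**What the claim requires, against what the data contain.**

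- The blind is claimed for the data as a whole (Secondary outcomes; Statistical analysis).
- Those data include the number of manual adjustments (Secondary outcomes), expected to be lower with CLAC (Abstract; Background).
- They also include outcomes derived from ventilator downloads (Data collection), where FiO2 is under software control in one arm only (Intervention). That the downloads show the arm is an inference from the method of control; the article does not state it.
- Duration of ventilation carries no such mark. Whether it differs by arm is the trial's question.

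**How far the adjustment counts identify the arm.** The documents give no adjustment rates, so these are assumptions: counts lognormal, ratio r of CLAC to manual between 0.2 and 0.5, between-infant coefficient of variation (CV) 0.5 or 1.0, and 35 infants per arm. The SD on the log scale is σ = √ln(1 + CV²), which is 0.472 for CV 0.5 and 0.833 for CV 1.0.

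- One infant, best single cut-off: P(correct) = Φ(−ln r / 2σ).
- Two coded arms, comparing mean log counts: P(right order) = Φ(−ln r / (σ√(2/35))).

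| r | CV | One infant classified correctly | Coded arms in right order |
|---|---|---|---|
| 0.5 | 0.5 | 0.768 | >0.9999 |
| 0.5 | 1.0 | 0.661 | 0.99975 |
| 0.3 | 0.5 | 0.899 | >0.9999 |
| 0.3 | 1.0 | 0.765 | >0.9999 |
| 0.2 | 0.5 | 0.956 | >0.9999 |
| 0.2 | 1.0 | 0.833 | >0.9999 |

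For the least favourable row, −ln 0.5 = 0.693 and σ√(2/35) = 0.833 × 0.239 = 0.199. The ratio is 3.48, and Φ(3.48) = 0.9997.

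An individual count is only a moderate guide to the arm (66% to 96% correct), but the group comparison settles which code is which. The group comparison is what the planned analysis of this outcome produces.

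**Whether the primary outcome is reached.** The article does not say which outcomes are analysed first, whether the analyst receives traces or summaries, or how the arms are coded. If the primary analysis comes first, its blind survives. If the adjustment counts come first under the same code, it does not.

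**The case against.** The strongest reply is that the article condenses a longer protocol and that an analysis plan may exist. Coded arms, separate datasets and the order of analysis normally belong there, so their absence here is not an error. That stands. The point rests instead on a claim that is made, twice and without limit, and that the trial's own outcomes defeat. An analyst given only derived summaries would still have the adjustment counts.

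Manual changes are also allowed in both arms, so counts overlap between infants. That stands for single infants but not for the group comparison, unless the reduction is much weaker than assumed above.

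Stronger readings are tempting, and the documents do not support them:

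- *A reader might infer that the blind is already lost when the primary outcome is analysed.* No order of analysis is given, so this is a possibility and not a stated feature.
- *A reader might infer that an unmasked analyst could steer the primary result through the choice of test, and put an inflated type I error on it.* Picking the smaller of two two-sided p-values needs no knowledge of the arms; codes A and B suffice. Any inflation from that belongs to an unfixed test choice and does not measure unmasking. The stated rule also leaves little room if the data resemble the unit's own. With a lognormal of median 12 and mean 19 days (log SD √(2 ln(19/12)) = 0.959, an assumed shape) and 35 per arm, a Shapiro-Wilk test on the pooled data rejected normality in all 10,000 simulated trials. That leads to Mann-Whitney whether or not the analyst is blind.
- *A reader might infer that the analyst could reclassify extubations.* The primary outcome section defines failure objectively, as reintubation within 48 h, and nothing assigns that classification to the analyst.
- *A reader might call analyst blinding the only safeguard.* The Statistical analysis section also fixes intention to treat, no imputation, and a two-tailed Fisher test.

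**Conclusion.** The point holds in a limited form, and its severity is minor. The unlimited claim of a blind analyst cannot be kept for the number of manual adjustments, and probably not for the outcomes derived from FiO2 and saturation downloads. For the primary outcome the blind is at risk only if the same person sees those data first under the same arm code.

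The probability above 0.999 that the coded arms are told apart rests on assumed ratios and CVs; the direction of the difference is the protocol's own. No figure for harm to the primary result can be drawn from the documents. The sample size of 70 and the planned tests are unaffected.

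**What to change.** Amend the two sentences on blinding, under Secondary outcomes and Statistical analysis, to say that:

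1. the analyst is blind to arm for the primary and clinical outcomes only;
2. that analysis is run on coded arms and locked before the ventilator-derived and manual-adjustment data are linked to the dataset;
3. those data are then analysed under a different arm code, and that part is described as not blinded.

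If the full protocol or an analysis plan already sets this order, the two sentences need only the limit in item 1 and a reference to it.

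The cost is a short paragraph, a second dataset and a fixed order of work, which means slightly more data management. No extra infants, staff or measurements are needed.
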